### Inclusion criteria

•Diagnosis of suspected acute stroke•Within 24 h of symptom onset•Age≥18 years

### Rejection criteria

•Other diseases that lead to motor dysfunction (e.g., claudication, severe osteoarthritis, rheumatoid arthritis, and gouty arthritis)•Other diseases or psychosis that renders outcome assessments or follow-up unlikely to be possible•Known to be pregnant or lactating•Non-acute stroke [result from Computed Tomography (CT) or Magnetic Resonance Imaging (MRI)].

### Intervention measures

The quantitative research part of this study will be observational. Based on our observation of whether XNJI was intravenously administered within 24 h of onset in the prehospital ambulance setting, patients with acute stroke will be divided into two groups: the exposure group comprising patients who were intravenously administered XNJI and the nonexposure group comprising patients who were not. During the study period, all relevant data will be collected at the following timepoints to facilitate a continuous dynamic observation and evaluation: during the prehospital ambulance service; within 24 h of admission; day 3 after stroke onset; day 10 after stroke onset or the day of discharge; and 30 ± 3, 60 ± 3, and 90 ± 7 days after stroke onset. This research will not interfere with the actual diagnosis and treatment of the participants. The clinicians will make decisions regarding routine treatment options based on the patient’s specific circumstances. The routine stroke treatment will follow the current national guidelines for acute Is and ICH from the Chinese Society of Neurology.

### Main variables

All variables used for outcomes evaluation of efficacy and safety are abstracted from all relevant data collected during the observation period. The main variables of this study are listed in Table 1.

**TABLE 1 T1:** Main variables registered in the TRACE study.

Field	Variables
Visit 1 (during pre-hospital ambulance service)	
Demographics information	Name; Age; Gender; ID number
Condition, state of consciousness, and survival or death upon ambulance arrival	Time of symptom onset; Time of ambulance arrival; State of consciousness; Survival/death; Stroke assessment (BEFAST)
Usage of XNJI	Use it or not; Time of first use of XNJI; Dose
Concomitant medication	Antihypertensive drugs; Vasopressor drugs; Hypoglycemic agent; Glycemic drugs; Other drugs
Auxiliary examination	Vital signs
Indicators on health economics	Treatment costs; Inspection fees; Medicine costs; Other costs; Total costs
Prehospital evaluation	NIHSS
Visit 2 (within 24 h after admission)	
Condition, state of consciousness, and survival or death upon arrival	Time of onset, Time of arriving at the hospital; State of consciousness; Survival/death
Baseline information	Height; Weight; BMI; Being overweight or obese; Predisposing factors; Transient symptoms occurred within 2 months before stroke onset; Past medical history (strokes; CHD; atrial fibrillation; diabetes; hypertension; hyperlipidemia; apnea); Personal history (smoking; alcohol consumption); Family history; Drug allergy history; Treatment history within 2 weeks before admission
Auxiliary examination	Vital signs; Laboratory tests; Cranial CT or MRI; ECG
Complication	Lung infections; Urinary tract infections; Upper gastrointestinal bleeding; Hiccups; Dysphagia; Urine retention; Urinary incontinence; Pressure ulcers; Kidney failure; Pulmonary embolism; Epilepsy; Shoulder-hand syndrome; Post-stroke depression; Post-stroke anxiety; Others
Admission evaluation	mRS; NIHSS; ICH Scale and GCS for ICH
Visit 3 (day 3 after symptom onset)	
Auxiliary examination	Vital signs
Complications	Lung infections; Urinary tract infections; Upper gastrointestinal bleeding; Hiccups; Dysphagia; Urine retention; Urinary incontinence; Pressure ulcers; Kidney failure; Pulmonary embolism; Epilepsy; Shoulder-hand syndrome; Post-stroke depression; Post-stroke anxiety; Others
In-hospital evaluation	NIHSS; ICH Scale and GCS for ICH
Visit 4 (day 10 after symptom onset or the day of discharge)	
TOAST classification of AIS	Major artery Atherosclerotic stroke; Cardiogenic cerebral embolism; Arterial occlusive stroke or lacunar stroke; Ischemic stroke resulting from other causes; Unknown cause of ischemic stroke
Major treatment methods	IVT and EVT for AIS; Surgery (craniotomy hematoma removal; minimally invasive surgery; bone valve decompression; ventricular drainage) and others for ICH
In-hospital medication	Antihypertensive agents; Hypoglycemic agents; Lipid-lowering drugs; Anticoagulants; Hemostatic agents; Reduced cranial pressure agents; Anticoagulants agents; XNJI (start use time; stop use time; use frequency; administration duration time; dose); Other TCM (Chinese patent medicine injection agent; Chinese patent medicine oral agent; TCM soup agent)
In-hospital rehabilitation	Acupuncture and moxibustion; Massage; PT; OT; ST; Others
Auxiliary examination	Vital signs; Laboratory tests; Cranial CT or MRI; ECG
Complication	Lung infections; Urinary tract infections; Upper gastrointestinal bleeding; Hiccups; Dysphagia; Urine retention; Urinary incontinence; Pressure ulcers; Kidney failure; Pulmonary embolism; Epilepsy; Shoulder-hand syndrome; Post-stroke depression; Post-stroke anxiety; Others
Indicators on health economics	Hospitalization costs; Treatment costs; Inspection fees; Medicine costs; Other costs; Total costs; Number of days of hospitalization
Discharge diagnosis	
In-hospital mortality	
Discharge evaluation	NIHSS; ICH Scale and GCS for ICH
Visit 5 (day 30 ± 3 after symptom onset)	
Follow-up evaluation	mRS; BI
Visit 6 (day 60 ± 3 after symptom onset)	
Follow-up evaluation	mRS; BI
Visit 7 (day 90 ± 7 after symptom onset)	
Basic medication	Antithrombotics agents; Anticoagulants agents; Lipid-lowering drugs; Antihypertensive agents; Hypoglycemic agents; TCM
Rehabilitation	Acupuncture and moxibustion; Rehabilitation exercise
Follow-up evaluation	mRS; BI
AEs (during the observation period)	Start time; Symptoms/signs; Intensity; Attack frequency; Duration and termination time; Laboratory indicators; Treatment methods and outcomes; Follow-up results

Note: Field and variables not specifically specified will be applied to all acute stroke patients (IS and ICH). Abbreviations: TRACE, The Trial of a prehospital intervention with traditional Chinese medicine for acute stroke; ID, identity card; BEFAST, Balance-Eyes-Face-Arms-Speech-Time; XNJI, Xingnaojing Injection; NIHSS, National Institutes of Health Stroke Scale; BMI, Body Mass Index; CHD, Coronary Heart Disease; CT, Computed Tomography; MRI, Magnetic Resonance Imaging; ECG, electrocardiogram; mRS, modified Rankin Scale; ICH, intracerebral hemorrhage; GCS, Glasgow Coma Scale; TOAST, Trial of Org 10172 in Acute Stroke Treatment; IVT, intravenous thrombolytic therapy; EVT, endovascular treatment; TCM, traditional Chinese medicine; PT, Physical therapy; OT, Occupational therapy; ST, Speech training; BI, Barthel Index; AEs, Adverse Events.

### Data collection and management

Through a prospectively designed electronic case registration form (eCRF), trained ambulance doctors will collect the prehospital diagnosis- and treatment-related information of the patient and will perform assessments using the National Institute of Health Stroke Scale (NIHSS) score through a face-to-face interview within 24 h after stroke onset during the prehospital ambulance service. Trained researchers appointed at each participating site will collect in-hospital data as follows: conditions state of consciousness, and survival or death on the day of admission; baseline information on the day of admission; the Trial of Org 10172 in Acute Stroke Treatment (TOAST) classification of AIS; major treatment methods; in-hospital medication; rehabilitation; auxiliary examination; complication; in-hospital mortality; discharge diagnosis and Indicators on health economics; they will also perform assessments using the NIHSS scale, ICH scale, Glasgow Coma Scale (GCS), and mRS during a face-to-face interview during hospitalization.

In this study, the data entry process will be refined, and different responsibilities and authorities of prehospital and in-hospital personnel will be emphasized. In the prehospital ambulance setting, the researcher will need to record the prehospital ambulance data of the patient promptly and fill in, complete, and submit the prehospital module before arriving at the hospital to hand over to the patient. Once the patient is admitted to the hospital, the information collected in the prehospital ambulance setting will be submitted by default and will not be modified again. After admission, the researcher in the receiving hospital will record the diagnosis and treatment data in the hospital timely, accurately, completely, and clearly in the eCRF according to the original observation record. Case registration must be completed for each selected patient; data collection and management will be conducted using an electronic data capture (EDC) system (http://1-dao.net:13579); the researchers and research assistants are responsible for data entry and submission by logging in the mobile terminal information platform. If the clinical supervisor has questions regarding the data recorded in the eCRF, the research assistants will consult with the researchers, who will answer and return as soon as possible, and then modify, confirm, and input the data. The research assistant will assist in completing the q & A work and fill out the data entry Q & A form. If the data collected after admission are found to be incorrect, modifications can be made with the help of a form comprising online questions and answers; the supervisor will thoroughly check all the data, raises questions, and coordinate with the researchers to resolve any concerns. The main goal of the verification process is to confirm whether data collection via the eCRF is timely, complete, objective, and accurate. The consistency of data and source files (photo of uploaded laboratory examination/function check report) will be checked, and a clinical explanation will be sought in case of any laboratory abnormalities. The supervisor will also check whether modifications of data collected through the eCRF comply with the specifications and note the reason for the modification; further, the collected data will be reconfirmed to ensure no logic errors. The electronic data entry system is set up with the necessary legal values and logical verification rules, whereby it alerts the researcher in case of possible outliers or data logic errors. The supervisor will regularly send data-related questions to the researchers in the participating centers and will follow up regarding the completion of the responses. After completing the data entry, the researcher will upload the data to the data center. The study data will be downloaded from the data center and transferred to the research team leader, sponsor, and statistical analyst. Written records of all the data handover processes will be maintained. The responsible unit and statistical analyst will lock the data, and no further revisions will be performed. Problems found after data locking will be corrected in the statistical analysis program after confirmation. Finally, after all the research data are entered and locked, the database will be submitted to the statistical analysts, who will perform statistical analyses according to the requirements outlined in the statistical plan.

### Follow-up procedures

Independent interviewers with a background in neurology will be trained in a standard operating procedure (SOP) for contacting patients. The interviewers will regularly follow up with the patients over the telephone using standard interview forms in the eCRF at 30 ± 3, 60 ± 3, and 90 ± 7 days after stroke onset. The standard interview forms in the eCRF include the mRS, BI, basic medication-related questions, and rehabilitation-related questions. All interviews will be recorded and saved. Patients will have the right to withdraw from the trial at any time without reason, punishment, or loss of interest, and their medical treatments will not be affected. Participants who do not formally withdraw from the trial but no longer attend follow-up sessions will also be regarded as having withdrawn from the trial. The data of these participants will be considered valid and will not be replaced. While respecting the individual rights of the participants, researchers should try their best to understand the reasons for withdrawal to better protect the participants. The participants who drop out due to AEs should be followed up until their physical status is stable, while the other participants who dropped out should not be followed up.

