### Types of outcomes

#### Efficacy outcomes

The primary outcome is END on the third day of onset defined as an increase of 2 or more points in the NIHISS score between baseline and day 3. The secondary outcomes include the rates of stroke-related and any-cause deaths during hospitalization, differences in the changes in the neurological deficit degree, risk grade of ICH evaluated through changes in the ICH scale score from baseline to day 10 or the day of discharge, the proportion of patients with activities of daily living with a Barthel Index score of ≥90, and the proportion of independent patients defined by a modified Rankin Scale score ≤2 at 30 ± 3, 60 ± 3, and 90 ± 7 days after stroke onset. A complete list of the efficacy outcomes analyzed in the TRACE study is presented in Table 2.

**TABLE 2 T2:** | The complete list of efficacy outcomes analyzed in the TRACE study.

Primary outcome
1. Early neurological deterioration# change
Early neurologic deterioration (END) is defined as an increase of 2 points or more in the National Institute of Health Stroke Scale (NIHSS) score between baseline and 3 days. The NIHSS score ranges from 0 (best score) to 42 (worst score). [Time Frame: between baseline and 3 days]
Secondary outcomes
1. Rate of stroke-related deaths and deaths from any cause Rate of stroke-related deaths and deaths from any cause during hospitalization [Time Frame: during hospitalization] 2. Neurological deficit Comparison of the change of degree of neurological deficit evaluated by the NIHSS [Time Frame: baseline and day 10 or the day of discharge] 4. Risk grade of a cerebral hemorrhage Comparison of the change of risk grade of Intracranial hemorrhage evaluated by Intracerebral Haemorrhage (ICH) scale. The ICH score ranges from 0 (best score) to 6 (worst score). [Time Frame: baseline and day 10 or the day of discharge] 5. Activities of daily living Activities of daily living will be measured by Barthel Index (BI) score. The proportion of patients with a BI score of ≥ 90. The BI score ranges from 0 (worst score) to 100 (best score). [Time Frame: 30, 60, and 90 days] 6. The proportion of patients’ independent The proportion of patients’ independence is defined as a modified Rankin Scale (mRS) score of ≤ 2. The mRS score ranges from 0 (best score) to 6 (worst score). [Time Frame: 30, 60, and 90 days]

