### Data processing and analysis

The mean (Mean), standard mean difference (SD), median (Median), interquartile ranges, minimum (Min), and maximum (Max) will be used to summarize continuous data, while rate or percentage will be used for categorical data. Between-group comparisons will be conducted using parametric or non-parametric tests, as appropriate. Pearson’s chi-squared test is used for the count data, and the results are expressed as rate or percentage (%). Measured data, if data are normally distributed and the variance is homogeneous, the parametric test (*t*-test) will be used and results will be expressed as mean ± SD; If the data are not normally distributed and still do not meet the requirements for the parametric test after data conversion, the non-parametric test (Wilcoxon rank sum test or Mann-Whitney U test) will be used and results will be expressed as median (Median).

As the primary analysis, a comparison of the presence of END on the third day after stroke onset will be conducted between the two groups of patients—the exposure group and the nonexposure group—using Pearson’s chi-squared test. The secondary outcome analyses will involve the rate of stroke-related and any-cause deaths, differences in the NIHISS scores, differences in the ICH scale scores, proportion of patients with BI scores ≥90, and proportion of patients with mRS scores ≤2. These analyses will be performed according to the standard statistical principles for comparing parametric or non-parametric distributions, as appropriate. During the analysis, multivariate linear regression analysis is performed for the influencing factors that are statistically significant in the univariate analysis. The full analysis set will be used in the efficacy correlation analysis in this study. The safety analysis set will be used in the safety analysis. The full analysis set refers to the set of eligible cases and detached cases but not eliminated cases. The safety analysis set will consist of safety indicators for all enrolled subjects with post-medication safety evaluation data; the number of subjects with missing data will be reported. All statistical tests will be one-sided, and statistical significance will be set at *p* < 0.05. SAS software, version 9.2 (SAS Institute, Inc., Cary, NC, United States), will be used to perform the statistical analyses.

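### Patients who stop attending without withdrawing consent are treated as withdrawn and not followed up, so their 30/60/90-day mRS and BI are avoidably, and possibly informatively, missing

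*Protocol article*

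**What the plan says.** Under Follow-up procedures, trained independent interviewers telephone patients "at 30 ± 3, 60 ± 3, and 90 ± 7 days after stroke onset" and collect mRS and BI. The same section then sets these rules:

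- Participants who have made no formal withdrawal but "no longer attend follow-up sessions will also be regarded as having withdrawn from the trial".
- Values already collected from such people are kept: "The data of these participants will be considered valid and will not be replaced".
- When someone leaves, staff are asked to find out why: "researchers should try their best to understand the reasons for withdrawal to better protect the participants".
- Leaving because of an adverse event has its own rule: "The participants who drop out due to AEs should be followed up until their physical status is stable".
- For everyone else who leaves, the instruction reads "while the other participants who dropped out should not be followed up".

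Under Efficacy outcomes, the secondary outcomes include "the proportion of independent patients defined by a modified Rankin Scale score ≤2 at 30 ± 3, 60 ± 3, and 90 ± 7 days" and the proportion with BI ≥90 at the same times. These are numbers 5 and 6 in Table 2. Under Data processing and analysis, "The full analysis set refers to the set of eligible cases and detached cases but not eliminated cases".

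**The concern.** Withdrawal of consent and failure to attend are different events. The first obliges the study to stop. The second leaves consent intact, and a patient who was not reached at one time may be reachable later. The protocol merges the two and tells staff not to follow up the non-adverse-event cases. That is an explicit instruction, not a detail left to the analysis plan, and no analysis can recover values that were never collected.

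At stake is the study's only planned efficacy evidence after discharge. Patients who stop answering may differ from those who continue, and exposure is not randomised, so equal attrition in the two groups cannot be presumed. If loss depends on outcome, the reported proportions are distorted. If that dependence also differs by exposure, so is the comparison.

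**Working it through.** **Step 1: combine the rules.** Stopping attendance without formal withdrawal counts as withdrawal. Dropouts for reasons other than adverse events are not followed up. Hence a non-attender with no adverse event gets no further outcome follow-up, although contact was never refused. This takes withdrawn and dropped out as the same status, which is how the paragraph uses them.

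**Step 2: does the adverse-event exception rescue the outcomes?** No. That follow-up ends when the patient is stable. It is not stated to run to day 90 or to include mRS or BI.

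**Step 3: which outcomes are exposed?** END is assessed at day 3, deaths during hospitalization, and the NIHSS and ICH-scale changes by day 10 or discharge. Only outcomes 5 and 6 depend on the telephone calls.

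**Step 4: how is a later death captured?** Table 1 has survival/death fields at Visits 1 and 2 and in-hospital mortality at Visit 4. For Visits 5 to 7 it lists only mRS and BI under evaluation. Apart from adverse-event records, a death after discharge enters as an outcome only through the worst mRS value, 6. A patient who has died also stops answering, so the rule could class that patient as withdrawn.

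**Step 5: size.**

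*The plan's own allowance.* The Sample size calculation section raises 852 to 1,000: 1,000/852 = 1.174, the stated 17%. The increment is 1,000 − 852 = 148, or 148/1,000 = 14.8%. If all 148 were lost, worst-case bounds on a 90-day proportion would be 14.8 points wide; for example, with 60% observed they run from 0.60 × 0.852 = 51.1% to 51.1% + 14.8% = 65.9%. But the section gives uneven exposure as a further reason for the increase, so 148 is not a loss forecast.

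*Illustration A (all values assumed).* Loss is 10% in one group and 20% in the other, and independence is 60% among those retained in both.

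- Lost patients 40% independent: true rates 0.9 × 60 + 0.1 × 40 = 58% and 0.8 × 60 + 0.2 × 40 = 56%. Observed 60% and 60%. The difference shifts by 2 points.
- Lost patients 30% independent: 0.9 × 60 + 0.1 × 30 = 57% and 0.8 × 60 + 0.2 × 30 = 54%. The difference shifts by 3 points.
- Each group's rate is overstated by 2 to 6 points.

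*Illustration B (all values assumed).* True independence is 60% in both groups. With g the fraction lost among good outcomes and b among poor ones, observed rate = 0.6(1−g) / [0.6(1−g) + 0.4(1−b)].

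| g | b | Observed |
|---|---|---|
| 15% | 15% | 0.51/0.85 = 60.0% |
| 10% | 20% | 0.54/0.86 = 62.8% |
| 5% | 30% | 0.57/0.85 = 67.1% |
| 20% | 10% | 0.48/0.84 = 57.1% |

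Row 2 in both groups gives no false difference. Row 2 against row 1 gives 2.8 points, and row 3 against row 1 gives 7.1 points. Row 4, where recovered patients are the ones who stop answering, reverses the direction.

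Both illustrations count all loss. The rule's own effect is smaller, because it concerns only patients whom a later call would have reached.

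**The case against.** The strongest reply is that the text is milder than it first looks, and much of that stands.

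- A reader might infer that one missed call ends follow-up, so that a patient missed at day 30 is never called at day 60 or 90. The wording describes ceasing to attend sessions, in the plural, and the sample size section expects patients who do not make every visit. The threshold is unclear; a single miss is not stated as the trigger.
- A reader might infer that all contact is forbidden. Researchers must still try to learn why a participant left, which may involve contact and could reveal a death. What stops is outcome follow-up.
- A reader might infer that having an adverse event decides who supplies 90-day outcomes. Step 2 shows that the text does not support this.
- Nothing says that a death is coded as withdrawal. It is a possible result of the rule, not a stated one.
- Data already collected are kept, and detached cases stay in the full analysis set. True, but keeping a patient in the set does not supply a day-90 value.
- The interviewers' operating procedure is not shown and may specify repeated call attempts. It may, but the published instruction not to follow up these participants would still have to be reconciled with it.

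None of this removes the core: people who have not refused contact are treated like those who have.

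**Conclusion.** The concern holds in a limited form. The follow-up rule makes some day-30, day-60 and day-90 mRS and BI values avoidably missing for participants whose consent still stands, and that missingness may be informative. The effect is confined to secondary outcomes 5 and 6, so this is a change that should be made, not one on which the primary analysis depends.

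It is tempting to conclude that outcomes are lost selectively and that the independence proportions are overstated. The documents do not support that as fact. They give no attendance by outcome or by exposure, the direction could go either way, and a false group difference needs outcome-dependent loss that differs between groups. The 2 to 3 points of illustration A, and the wider range of B, rest entirely on assumed loss rates and do not measure the rule's own effect.

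**What to change.** In Follow-up procedures and the interviewers' operating procedure:

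1. Define formal withdrawal or refusal of contact separately from non-attendance.
2. Attempt every remaining scheduled 30-, 60- and 90-day call for anyone who has not refused contact, whatever the reason for dropout.
3. Record death as mRS 6 whenever it is learned.
4. Analyse all outcomes obtained.

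Leave the existing safety follow-up of adverse-event dropouts unchanged; the new rule concerns outcome calls only.

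The cost is a few sentences and some extra calls by interviewers already in place. The limit is timing. Recruitment began in March 2018 and was expected to end in December 2022, and the article appeared in August 2022, so the change reaches only patients not yet past day 90. Two follow-up rules would then coexist in one cohort, so the date of the change should be recorded.
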